## Abstract

Innovative technologies can support older adults with or without disabilities, allowing them to live independently in their environment whilst monitoring their health and safety conditions and thereby reducing the significant burden on caregivers, whether family or professional. This paper discusses the design of a study protocol to evaluate the acceptance, usability, and efficiency of the SAVE system, a custom-developed information technology-based elderly care system. The study will involve older adults (aged 65 or older), professional and lay caregivers, and care service decision-makers representing all types of users in a care service scenario. The SAVE environmental sensors, smartwatches, smartphones, and Web service application will be evaluated in people’s homes situated in Romania, Italy, and Hungary with a total of 165 users of the three types (cares, elderly, and admin). The study design follows the mixed method approach, using standardized tests and questionnaires with open-ended questions and logging all the data for evaluation. The trial is registered to the platform ClinicalTrials.gov with the registration number NCT05626556. This protocol not only guides the participating countries but can be a feasibility protocol suitable for evaluating the usability and quality of similar systems.

## 1. Introduction

In 2050, there will be 1.5 billion people aged 65 worldwide [1]. The central policy in response to this global trend is to foster the concept of Active and Healthy Ageing (AHA) [2,3]. Despite the influence of genetics, the health of the older population is associated mainly with the physical and social environments of their daily life, such as homes, neighborhoods, and communities, and of their individual characteristics, such as gender, ethnicity, and socioeconomic status [4,5].

Innovation technologies can support older adults, with or without disabilities, by enabling an independent life in their environment and monitoring their health status and safety, therefore reducing the significant burden of care for caregivers, whether family and/or professional [6,7,8]. Using smart artifacts can also be an effective way to overcome social isolation through connecting with the outside world, obtaining social support, engaging in activities of interest and strengthening self-confidence [9,10,11,12]. In addition, innovative technologies can improve the safety of older people through emergency solutions (e.g., fall detection, alert function, help call opportunities) by supporting therapy, observing physical parameters, and controlling the environmental ones [13,14,15,16,17]. Khosravi et al. [18] reported that key issues in aging care are the risk of falls, chronic diseases, dementia, social isolation, depression, poor well-being, and insufficient medication management. He raises the point that assistive technologies can improve the quality of life, especially among older adults, by tackling each of the issues previously outlined.

Although there is limited understanding of the digital landscape for aging care [19], several Smart Home technologies (e.g., web platforms, applications, sensors) that support older adults’ quality of life, security, and growing sense of loneliness have been developed in recent years. The success of these technologies still depends on users’ perception of personal privacy [20], so data security and confidentiality are a priority for the acceptance of a Smart Home system. To address these challenges, several projects have been developed. For example, after a 12-week Smart Home personalized technology program, participants’ quality of life increased significantly [21], the Fik@ room web platform allowed social connection among older adults in a secure digital environment [22], and the SMART4MD mobile application [23] facilitated a sense of coherence for older persons with cognitive impairment.

The COVID-19 pandemic has had an enormous impact on the extent of social connectedness and the quality of relationships among individuals, and it will probably represent a general rethinking of new methods and (digital) models of care [19]. Different approaches for the involvement of older people in various activities and reducing social isolation have been proposed in the last two years [24]. The Pharaon Project [25] addressed the importance of alternative approaches to face-to-face methods using phone and online interviews, online questionnaires, and virtual and semi-virtual co-creation seminars. Moreover, telemedicine and e-Health services have proven essential to support care for older adults and family caregivers. For example, Internet-based technology has helped people at early stages of cognitive impairment through electronic reminders, daily activities, and cognitive stimulation therapy and games [26].

Based on this scenario, eight partners from three countries (Italy, Hungary, and Romania) joined their efforts in the European-funded SAVE (SAfety of elderly people and Vicinity Ensuring) project (EU Grant Agreement AAL-CP-2018-5-149). The SAVE system aims to offer technology-based support to older adults to stay in their familiar surroundings for as long as possible while feeling safe and optimally cared for. The SAVE technology has been designed and developed according to the User Centered Design (UCD) approach, which involves multiple interactions with users to understand their needs and preferences and involve them in the design process for creating a helpful and appreciated technological product [27]. Secondarily, it supports informal caregivers, such as relatives, in providing optimal care for their loved ones while maintaining their professional and private life.

### Study Objectives

The general objective of this study is to test the usability and efficiency of the SAVE prototype by systematically and objectively identifying the strengths and weaknesses of the proposed solution for enabling older adults to keep their independent and active lives in their homes and maintain their social relationships for as long as possible.

## 2. Methodology

### 2.1. Study Design

To thoroughly evaluate the SAVE prototype, a pre-post interventional study involving the use of the SAVE platform for 21 consecutive days was designed. It consists of the use of a mixed-methods approach, in which it collects both qualitative (open questions) and quantitative (standardized tests) data in three different measurements (T0, T1, T2) during the period of use of the system. The data collection card will therefore be divided into three different sections, which correspond to the three different moments of detection:Prior to the start of the experimentation (T0);Ten days into the intervention study, i.e., at the midterm of the trial (T1);After 21 days, i.e., at the end of the trial (T2).

The users’ data will be logged and continuously stored over the 21-day test period. The research will be managed by qualified personnel, and the researchers will supervise the tests and the interactions between the users and the system.

### 2.2. Study Setting

The study involves three different European institutions in charge of performing the feasibility assessment: the Istituto di Ricerca e Cura a Carattere Scientifico, Istituto Nazionale Ricovero e Cura Anziani (IRCCS INRCA located in the city of Ancona in Italy, the National Institute for Medical Rehabilitation (NIMR) in the city of Budapest in Hungary and the Transilvania University of Brașov (UNITBV)in collaboration with the Romanian Direction of Social Assistance (DAS) located in the Brasov City Council and the Timișoara City Council and with ”Hand in Hand” Association from Brașov in Romania. This multicentric setting will allow for assessing the SAVE system in different social and cultural contexts. Overall, the cross-national approach will ensure a broad acceptance of the developed technology and prepare the possibility of its dissemination and the transferability of the research methods adopted by the SAVE study at the European level and well beyond the initial life cycle of the project.

### 2.3. Participants

The study will involve primary, secondary and tertiary users. According to the European Project SAVE activities, the primary users are expected to be 80 older adults: 30 participants will be enrolled in Romania, 25 in Hungary and the remaining 25 in Italy. Their caregivers (30 participants will be enrolled in Romania, 25 in Hungary and 25 in Italy) as secondary users and at least 5 tertiary users for the site will be enrolled.

Inclusion and exclusion criteria for each end user group are described in Table 1.

### 2.4. Recruitment

Potential participants will be selected based on free participation and effective adherence to the inclusion criteria. The staff involved in the study will contact their networks (associations, recreational centers, trade unions, etc.) by phone and/or email, which will provide the names of potential participants. The latter will be contacted by phone to verify the inclusion criteria and describe the objectives, methods, procedures and timing of the study. Once compliance with the inclusion and exclusion criteria of the study is verified and informed consent is obtained, the local team member will proceed with the baseline evaluation. 

### 2.5. Trial status

User recruitment was started in (enter date here), which was completed by (enter method here). The study is currently underway, with data collection beginning in September 2022 and expected to end by March 2023.

### 2.6. The Intervention

The SAVE system will be implemented in end users’ homes, which is achieved by installing all the kits in the appropriate rooms and by offering relevant training for using all the different devices to the end-users.

Flood sensors will be installed in the bathroom (preferably next to the washing machine) and kitchen (preferably next to the dishwasher), presence sensors in the living room and bedroom, and the contact sensor will be installed at the entrance door. The sensors are powered by button batteries with very low energy consumption; the producer of the sensors advertises an autonomy of 2 years with a standard CR2032 button battery. Only the sensors’ hub and the SAVE Sensor Adapter are powered from a socket (the SAVE Sensor Adapter is powered by the USB connector on the sensors’ hub). The other devices can be used as long as they are charged (the smartwatch and smartphone). Thus, the end user’s responsibility is to charge their smartwatch and not to unplug the sensors’ hub (and, in Hungary, the smartphone from the charger). It is planned to place the central unit in the bedroom, where the user can easily charge the smartwatch in the evening. For the best user experience, the required software (for the sensors kit and the smartwatch) will be installed on the users’ smartphones in Romania and Italy. On the Hungarian side, users are provided with a separate mobile phone to receive data and transmit it to the cloud system.

The sensor set and the smartwatch software are only downloaded to the user’s mobile phone at the user’s request. The sensors have been located in places where they do not affect the daily activity of the users, these being easy to move according to preferences and small enough to blend in the background. Thus, at the end of the installation, users will have the Aqara Home System in their homes (5 sensors and a sensor hub), a Samsung smartwatch, and a SAVE Sensors Adapter, all of which are connected to a router with unlimited internet access.

After installing the system, there will be a brief instruction training session on the use and purpose of these devices and the services they offer. This will ensure that the end users are encouraged to use them, performing some tests with them:Heart rate testing in association with the frequency indicated on the smartwatch;Testing the emergency system by pressing the power button 3 times;Testing of the flood and door sensors by visualizing the values received by the SAVE cloud app through the SAVE Web App;Calling a friend/relative from their smartwatch.

To test the pilot solution, the following step-by-step guide will be followed:Kit creation (from the SAVE Admin Centre)—a unique kit key will be generated;Adding devices to the kit (1 x Save Sensor Adapter and 1 x Galaxy Watch 3);Checking the internet connection of the phone/home router in Romania/Italy and the provided mobile phone in Hungary);Verify that the user has a Gmail account; for those users who do not have an account, an account is created;User account creation (self-register—from the SAVE Web App) (Figure 1);Filling in the user profile, including the Kit Key;Installation of the Aqara Home app from the Play Store;Installation and placement of Aqara hub and sensors by following the instruction in the Aqara Home app (Figure 2);Test the functioning of all sensors through the Aqara Home app;Adding a remote control for the Sony projector from the Aqara Home app on the Aqara hub;Adding the SAVE automations in the Aqara Home app by following the instruction in the Aqara Home app and the SAVE installation manual (Figure 3);Installation and configuration of the SAVE Sensor Adapter using WPS or SWS (Figure 4); the SWS is performed by connecting the SAVE Sensors Adapter to a PC/laptop and using the SAVE Sensor Adapter Wi-Fi Setup application desktop application to set the Wi-Fi settings (Figure 5);Test the sensors through the SAVE Platform;Installation of Galaxy Wear app from the Play Store;Pairing the smartwatch to the Galaxy Wear app;Activate Debug mode on the smartwatch;Installation of the two smartwatch apps using the sdb tool provided by Tizen Studio (save-configuration.wgt and save-tizen-watch-face.wgt);Configure the smartwatch for SAVE by filling in the native ID into the SAVE configuration app (Figure 6);Setting the smartwatch face to the SAVE watch face (Figure 7);Configuration of the SOS and fall detection features from the Galaxy Wear app;Test the emergency system. Furthermore, test the data sent from the watch together with the data sent from home (Figure 8);Creation of caregivers’ SAVE Web accounts;Linking the caregivers accounts to the end-user account via the SAVE Web app.

On the Hungarian side, the 7th, 10–21 is completed just before the system is deployed.

### 2.7. The Outcomes

In accordance with the general objectives of this study, primary and secondary outcomes are described in the following subsections.

#### 2.7.1. The Primary Outcomes

The primary outcomes are:Usability, which is understood as “the extent to which a product can be used by certain users to achieve certain goals with effectiveness, efficiency, and satisfaction in a given context of use”. This result will be measured through the SUS scale [28] and the UEQ questionnaire [29].Learnability of the system, which is seen as a component of usability, is the degree to which an interface is intuitive, and the user can immediately understand how to interact with the system. This result will be measured through the SUS scale [28].Acceptance, seen as the degree to which users come to accept and use a piece of technology. This result will be measured through the SUS scale [28] and the UEQ questionnaire [29].

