System Usability Scale (SUS) [28] is a reliable tool for measuring usability. It consists of a 10-item questionnaire with five response options for respondents from ‘Strongly agree’ to ‘Strongly disagree’. It allows for evaluating various products and services, including hardware, software, mobile devices, websites, and applications. It is easy to administer to participants, can be used on small sample sizes with reliable results, and can effectively differentiate between usable and unusable systems.User Experience Questionnaire (UEQ-S) [29]. This short version of the questionnaire measures the subjective impression of users towards the user experience of products. The UEQ is a semantic differential with 26 items. Both classical usability aspects (efficiency, perspicuity, dependability) and user experience aspects (originality, stimulation) are measured.Quebec User Evaluation of Satisfaction with assistive Technology (QUEST—Version 2.0) [38] is a 12-item outcome measure that assesses user satisfaction with two components, Device and Services.
(D)Privacy and Stigmatization
Open questions

The data collection sheet for secondary users consists of a sequence of 5-Likert scale questions on the following dimensions (Table 2):Usefulness of the system,Reliability of the system,

and some free comments about satisfaction with the system.

The data collection sheet for tertiary users consists of a sequence of 5-Likert scale questions on the following dimensions (Table 2):Impact of the system on the reduction in time spent in caregiving activities;Impact of the system on the reduction in the cost of caregiving activities;Impact of the system on the reduction in the workload.

Each instrument will be administered, if possible, in a face-to-face session in the presence, otherwise remotely, of a trained interviewer, who will report the answers on a paper version of the data collection card.

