During use, the following log data will be continuously recorded: usage time/used services (time/number), number of interactions, participation in social events (web conference, phone call, video call), tracked daily activities, number of errors, number of aids required for the tasks, recognized user commands, used input modality, captured touch screen data/activity, number of services used in the given period, number of tasks solved by using the SAVE system (for example, did the user recieve an answer to a question, did the user manage to call/inform the caregiver, was the user able to perform recreational activities with the help of the device, did the user manage to send the alarm to the caregiver, whether the caregiver was informed about the user’s fell, could not sleep, decreased activity, be deteriorated, etc.).

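### Acceptance has the same instruments as usability and none that records use, and learnability is first read at day 10, while the logged use, errors and aids are linked to no outcome in section 2.7

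*Protocol article*

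**What the plan says.** Section 2.7.1 gives each primary outcome a definition and an instrument.

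- **Usability** is how far users can use the product "to achieve certain goals with effectiveness, efficiency, and satisfaction in a given context of use". For its measurement the article states: "This result will be measured through the SUS scale [28] and the UEQ questionnaire [29".
- **Learnability** is presented as a component of usability. It "is the degree to which an interface is intuitive, and the user can immediately understand how to interact with the system". The instrument is SUS alone.
- **Acceptance** is introduced as "Acceptance, seen as the degree to which users come to accept and use a piece of technology". The instruments are again SUS and UEQ.

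Section 2.8 describes SUS as a usability tool and UEQ as covering usability and user-experience aspects. It also describes QUEST 2.0, which "assesses user satisfaction with two components, Device and Services". Section 2.8 and Table 2 file QUEST 2.0 with SUS and UEQ-S under a joint usability and acceptance dimension, but section 2.7.1 does not mention it.

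Table 2 schedules SUS, UEQ-S and QUEST 2.0 at T1 and T2 only. Section 2.1 puts T1 ten days into the intervention and T2 at 21 days. Section 2.8 also lists log data recorded continuously during use, among them "usage time/used services (time/number), number of interactions", errors, and aids needed for tasks. Section 2.7 links none of these to an outcome.

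**The concern.** Two of the three primary outcomes have definitions that their measures do not reach.

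Acceptance is defined partly by behaviour, namely whether people come to use the system, but it is measured only by rating questionnaires. A participant who has stopped wearing the watch and one who wears it daily are distinguished only if they rate the product differently. The instruments are also identical to those for usability, so nothing in the stated plan makes an acceptance result different from a usability result.

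Learnability is defined by immediacy, but its first reading follows a training session and ten days at home. Someone who needed repeated help in the first days and coped by day 10 may show no difficulty.

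This matters in the population chosen. Table 1 admits older adults with MMSE between 21 and 27. Section 4.1 names low digital literacy and forgetting the instructions as foreseeable problems, and says the design will allow changes in behaviour regarding acceptance to be analysed. The acceptance measure in section 2.7.1 contains no behaviour.

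**Working it through.** The plan gives no figure on this point to reproduce. The check sets definition, instrument and timing side by side.

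| Primary outcome (2.7.1) | Key element of definition | Instruments (2.7.1) | First reading (Table 2, 2.1) |
|---|---|---|---|
| Usability | effectiveness, efficiency, satisfaction | SUS, UEQ | T1, day 10 |
| Learnability | intuitive, understood at once | SUS | T1, day 10 |
| Acceptance | accepting and using | SUS, UEQ | T1, day 10 |

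**Step 1: overlap of instruments.** Usability = {SUS, UEQ}, learnability = {SUS}, acceptance = {SUS, UEQ}. The acceptance set equals the usability set, and the learnability set is contained in it. The number of instruments unique to acceptance or to learnability is 0. Section 2.7.1 names no subscale, item set or scoring rule that would separate them.

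**Step 2: does the instrument reach the definition of acceptance?** As described in section 2.8, SUS measures usability and UEQ measures usability and user-experience aspects. Neither description mentions use of the system. The use half of the acceptance definition therefore has no assigned measure. Usage time, services used and interactions, which bear directly on it, are in the log.

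**Step 3: does the timing reach the definition of learnability?** The definition requires that "the user can immediately understand how to interact with the system". Section 2.6 places training, with hands-on tests, straight after installation. The first SUS comes at day 10 of 21: 10/21 = 0.476, or about 48% of the test period. SUS cannot sensibly be given at T0, before the user has the system, so its absence there is correct. The gap is that nothing between installation and day 10 is assigned to learnability, although errors and aids required are logged throughout (sections 2.1 and 2.8).

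**Step 4: QUEST 2.0.** Section 2.8 and Table 2 place it under usability and acceptance; section 2.7.1 omits it. The two places disagree. QUEST 2.0 measures satisfaction, which section 2.7.1 names in the definition of usability and not in those of the other two outcomes.

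**The case against.** The strongest reply is that item sets and scoring are commonly left to an analysis plan, that section 2.9 promises one, and that the log data already belong to the mixed-methods evaluation. Learnability is called a component of usability, so overlap with SUS is intended. A user can still judge after ten days how intuitive an interface is, and an acceptance process that develops over time suits readings at T1 and T2.

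Part of this stands. Reading learnability from SUS is not wrong in itself, and an analysis plan could name the items. But which instruments measure which primary outcome, and when, is fixed in section 2.7.1 and Table 2. An analysis plan cannot create an earlier SUS reading, and making use part of acceptance changes section 2.7.1 itself.

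A reader might infer more than the documents support:

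- *That QUEST 2.0 and efficiency are tied to no outcome.* QUEST 2.0 is filed under usability and acceptance in section 2.8 and Table 2. Efficiency is in the usability definition and is listed as a UEQ aspect.
- *That the three outcomes are one number, perfectly correlated.* That would need the SUS total to be the score for both usability and learnability. The article does not say so, and UEQ covers several aspects.
- *That acceptance will be overstated by the share of users who stop.* The article sets no threshold for counting someone as accepting, so there is no such proportion to inflate. How people who stop would rate the system is unknown.

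**Conclusion.** The point holds as a mismatch between the definitions and the assigned measures for two of three primary outcomes. Acceptance shares both of its instruments with usability and has no measure of use. Learnability has one instrument, also used for usability, first read after 10 of 21 days (48%) and after training. Followed as written, the trial cannot report acceptance separately from usability, and its learnability reading misses early difficulty.

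No numerical bias can be given. Missing abandonment and early difficulty could make the results look more favourable, but the documents do not show that it will or by how much. The conclusion rests on the instrument descriptions in section 2.8 and on no fuller document assigning other measures to these outcomes. The usability outcome itself is not in question. The change should be made, because the needed data are already being collected.

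**What to change.** Revise section 2.7.1 as follows.

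1. **Usability:** keep SUS and UEQ.
2. **Acceptance:** add a pre-defined, log-based measure of use. One option is continued active use of the watch or app to T2 among all users with the system installed, counting those who stop as non-users. Active use must be defined so that passive sensor data do not qualify, since door, presence and flood sensors report without any decision by the user.
3. **Learnability:** state in advance which of the ten SUS items, those on learning and needing help, form the score. The article does not reproduce the items, so the choice must be checked against the instrument. Support it with logged errors and aids required in the first days, counted from after the training session so that supervised tests are excluded.
4. **QUEST 2.0:** make section 2.7.1 and Table 2 agree on the outcome it serves.

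Section 2.5 says data collection is under way, so record this as a dated amendment made before the outcome data are analysed, leaving the existing questionnaire results to be reported as planned.

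The cost is rewording, a definition of active use and some log analysis, with no new assessments and no added burden on participants. The acceptance result may be less favourable than a questionnaire score alone.
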